More recently, a new family of interventions, collectively called Cognitive Bias Modification (CBM), has been developed to tackle prepotent, drug-evoked automatic processes involved in addiction [8,12,13]. CBM paradigms are computerised tasks aimed at training alternative responses to a drug-related stimulus in order to adjust the biases that underlie the breakdown in controlled processes. Typically, they are modified versions of assessment tasks, such as the Approach-Avoidance Task (AAT) [14,15], with a built-in contingency that recasts them to re-training paradigm.

The first clinical applications of CBM paradigms as an add-on to standard interventions such as cognitive behavioural therapy have shown promising results [16-19]. Two randomised controlled trials (RCTs) with German alcohol-dependent inpatients did demonstrate that an approach bias for alcohol stimuli could be re-trained, with a generalisation of the training effects beyond the experimental procedure context [18,19]. Moreover, participants in the training condition had a lower rate of relapsing within one year after discharge, after controlling for gender in Wiers *et al*. [18], and for age and number of previous detoxifications in Eberl *et al*. [19]. A study with Dutch alcohol-dependent inpatients showed the success of an attentional bias re-training in increasing the ability to disengage from alcohol stimuli, with a generalisation to untrained, new stimuli and a significantly longer time until relapse for the experimental group in the follow-up period [17].

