Additionally, we study whether CBM effectiveness is moderated by participant characteristics, namely interference control capacity and strength of the cognitive biases at pre-test. Individual differences in executive functioning can moderate whether the initial automatic reaction towards a glass of wine can be effectively and easily controlled or not. It has been suggested that prolonged alcohol use can negatively affect the deployment of reflective processes (such as interference control and working memory capacity [22,23]), thereby reducing the cognitive capacity available for controlling automatic impulses [8]. Hence, alcohol dependents with a relatively weak ability to inhibit a prepotent approach response (low interference control capacity) may find it more difficult to remain abstinent than those with a relatively strong ability to inhibit a pre-potent response. CBM interventions could be particularly beneficial for those who present relatively poor interference control capacity and/or strong automatic reactions demanding great control efforts. Therefore, in line with dual-process models of addiction and prior findings [8,18,19,24-26], it is expected that participants with strong automatic biases and/or weak interference control will benefit more from the CBM intervention than participants with weaker biases and/or stronger executive functions.

Finally, the effect of several independent clinical variables (such as age, gender and number of previous detoxifications) on the primary and secondary clinical outcomes will be explored, in particular the type of treatments participants are receiving alongside the CBM, such as medication intake and/or other psychotherapeutic interventions.

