### Baseline measures

Sociodemographic information (gender, birthdate, annual income and educational level) and clinical case history details (duration of alcohol addiction, previous detoxifications and treatments, duration of current abstinence and medication intake) are collected during participants’ research registration.

At the first baseline assessment session, other substance use (integration of CORE Alcohol and Drug Abuse Survey (CORE Institute) and the Italian Population Survey on Alcohol and other Drugs questionnaire (National observatory for Drug Use)), self-esteem (Rosenberg Self-Esteem Scale, RSES) [39,40], anxiety (State-Trait Anxiety Inventory-Y, STAI-Y) [41] and depressive symptoms (Beck Depression Inventory-II, BDI-II) [42] are evaluated. After the questionnaires, participants are assessed for baseline alcohol approach bias (VPT) and attentional bias (AAT).

At the second baseline assessment session, alcohol abuse (Alcohol Use Disorders Identification Test (AUDIT)) [43], craving (Obsessive-Compulsive Drinking Scale, OCDS) [44] and motivation to treatment (MAC2-A) [33] are evaluated.

After the questionnaires, a computerised version of the classical Stroop task [45,46] is used to assess interference control capacity [18,19,26]. In this task, participants have to classify words and symbols according to their ink colour and ignore the content. The task starts with a practice block, in which participants have to learn the correct key-colour combination (only neutral and incongruent trials are presented). The second block consists of a second practice block task with grey key reminders on the bottom of the screen. The third block is a test block composed of 112 trials in which the key reminders disappear and 16 neutral trials (such as symbols like #### in blue ink colour), 48 congruent trials (such as the word ‘red’ in red ink colour) and 48 incongruent trials (such as the word ‘red’ in yellow ink colour) are presented.

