### Data analysis

Complete analyses will be conducted in agreement with Intention-To-Treat principle [26]. Missing data points will be handled with multiple imputation.

To answer to the main research question, a multiple logistic regression will be used to estimate how much the main and combined exposure to the two CBM modules affects the occurrence of lapse and/or relapse episodes at the three-month follow-up assessment.

The secondary research question, whether participants approach and attentional biases do change after the CBM intervention, is addressed via a 3×2×3 repeated-measures mixed ANOVA with the AAT and VPT scores as dependent variables, time (baseline, post-intervention and follow-up) as repeated measures within-subject factor, drink type (alcoholic and non-alcoholic) or attentional process (engagement and disengagement) as within-subject factor, and CBM condition (re-training or placebo) as between-subject factor. The same analysis applies to the continuous secondary outcome measures administered at each time point.

The third research question of the present study is framed within a ‘what works best for whom?’ approach [8] and explores the moderating and mediating roles of individual differences variables on the clinical outcome by means of a moderated mediation analysis [51]. More precisely, baseline strength of the cognitive biases and interference control capacity (Stroop task), as well as age, gender and previous detoxifications, are hypothesised to moderate the change in cognitive bias after the CBM intervention, which is further hypothesised to eventually mediate the change in the clinical outcome variable (see Eberl *et al*. [19]).

Finally, participants’ motivation to change (MAC2-A) at pre- and post-intervention will be compared via a paired t-test. Via a repeated-measures ANOVAs we will explore whether change in participants’ motivation to carry on with the training after the brief MS interviews affects attrition and training outcome.

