### Sample size

The sample size is limited to 120 recruited participants due to constraints in the ratio between the number of potential participants fully meeting the eligibility criteria and available to participate in the study, out of the total number of alcohol-dependent outpatients currently in charge in the public service at the time of recruitment (3:10). Therefore, a realistic estimate of 120 participants (n = 30 per experimental condition) was considered achievable for a phase II RCT study, and further supported by a minimum number of cases identification analysis.

An operational guideline to identify the minimum number of cases to include in the study has been suggested by the Peduzzi *et al*. [52]. For *k* independent variables and *p* as the smallest of the proportions of negative or positive cases in the population, then the minimum number of participants is 10*k/p. Based on three previous CBM studies with alcohol dependent clinical populations, the average proportions of occurrence or absence of relapse event(s) at follow-up are about 0.53 and 0.47 after an approach bias or control re-training, respectively [18,19]; and about 0.40 and 0.28 after an attentional bias or control re-training, respectively [17]. The proportions were computed out of the total number of enrolled participants.

By taking the minimum among the four proportion values and setting *k* = 2 (two independent variables: attentional bias CBM re-training or placebo and approach bias CBM re-training or placebo), the minimum number of cases to be included in the present study is 10*2/0.28 ≅ 71. According to this approach, the proposed sample size is more than adequate to answer to the primary research question of the present study and should also allow for high attrition rates. It is worth noting that Wiers *et al*. [18] and Eberl *et al*. [19] had a one-year follow-up period, whereas Schoenmakers *et al*. [17] had a three-month follow-up period. The different follow-up timing allows only a partial comparison of the above-mentioned proportions. If similar proportions at one-year of follow-up were also observed in Schoenmakers *et al*. [17] then the minimum number of cases would decrease to 10*2/0.47 ≅ 43.

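### Naming age and number of previous detoxifications as covariates in the primary relapse model would be a cheap improvement, probably worth a few points of power

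*Protocol article*

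**What the plan says.** - **Primary model.** Under Data analysis, "a multiple logistic regression will be used to estimate how much the main and combined exposure to the two CBM modules" affects relapse at three months. No baseline covariate is named.
- **Predictor count.** Under Sample size, the minimum-cases rule is applied with k = 2, explained as "two independent variables: attentional bias CBM re-training or placebo and approach bias CBM re-training or placebo". The detectable odds ratio comes from a simple logistic regression, one module at a time.
- **Role of the two variables.** The aims section says that the influence of "several independent clinical variables (such as age, gender and number of previous detoxifications) on the primary and secondary clinical outcomes will be explored". Under Data analysis the same variables, "as well as age, gender and previous detoxifications, are hypothesised to moderate the change in cognitive bias after the CBM intervention". The Abstract lists them as possible moderators in an exploratory analysis.
- **Availability.** Under Baseline measures, birthdate and "previous detoxifications and treatments" are recorded at registration.
- **Precedent.** The Background says that in two inpatient trials of approach-bias training "participants in the training condition had a lower rate of relapsing within one year after discharge", in one of them after controlling "for age and number of previous detoxifications" and in the other after controlling for gender.
- **Allocation.** Under Randomisation, the balancing factors are gender and medication category. Age and previous detoxifications are not among them.

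**The concern.** The trial cannot easily buy power by recruiting more patients. The Sample size section caps enrolment at 120 because eligible patients are scarce, and the Discussion concedes a possible drawback in power. The detectable odds ratio of 0.396 is a large effect, and it rests on a one-tailed test.

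Covariates that predict relapse would sharpen the comparison at no recruitment cost. Two candidates are already collected and were used for this purpose in a trial the article cites. Since allocation does not balance them, a chance difference between arms of about 60 also goes unaddressed in the main result. Naming them beforehand would settle which analysis is primary before anyone sees an adjusted result.

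**Working it through.** **1. Inputs.** From the Sample size section: n = 120, so 60 v 60 per module; placebo relapse 0.60; odds ratio 0.396; power 0.80; one-tailed test with critical z of 1.645 in absolute value; minimum-cases rule 10·k/p. The article gives no strength of association between relapse and age or previous detoxifications, so this is varied as an assumption.

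**2. The plan's own figure.** Active-arm odds = 0.396 × 0.60/0.40 = 0.594, so the active rate is 0.594/1.594 = 0.3726.

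- Wald: |ln 0.396| = 0.926. SE = √[1/(60 × 0.60 × 0.40) + 1/(60 × 0.3726 × 0.6274)] = 0.375. Power = Φ(0.926/0.375 − 1.645) = 0.795, with a detectable odds ratio of 0.393.
- Two proportions: power 0.808, with a detectable odds ratio of 0.400.

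The stated 0.396 lies between these, so it reproduces. A two-sided 5% test gives only 0.69 to 0.71.

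**3. Effect of adding two covariates.** Trials were simulated from logit P(relapse) = a₀ + (a₁ − a₀)·module + b·(c₁ + c₂). Here c₁ and c₂ are independent standard normal covariates and exp(b) is the assumed odds ratio per SD. The values a₀ and a₁ were solved so that the marginal rates stay at 0.60 and 0.3726. The other module had no effect. There were 8,000 trials per row, each analysed both with and without the covariates by a one-sided Wald test.

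| Assumed OR per SD, each covariate | Conditional module OR | Power, unadjusted | Power, adjusted |
|---|---|---|---|
| 1.00 | 0.396 | 0.807 | 0.808 |
| 1.24 | 0.388 | 0.813 | 0.817 |
| 1.42 | 0.375 | 0.809 | 0.830 |
| 1.70 | 0.353 | 0.808 | 0.846 |
| 2.03 | 0.327 | 0.813 | 0.866 |
| 2.89 | 0.271 | 0.810 | 0.910 |

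Monte Carlo error is about ±0.9 points per figure (95%). Repeat simulations gave:

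- 0.81 to 0.82 at an odds ratio of 1.3;
- 0.81 to 0.83 and 0.81 to 0.84 at 1.5;
- 0.79 to 0.85 and 0.80 to 0.87 at 2.0.

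Type I error of the adjusted test stayed near 5% even at a 28% event rate.

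**4. The same gain in patients.** By the normal approximation, going from 0.809 to 0.830 multiplies the effective n by [(1.645 + 0.954)/(1.645 + 0.874)]² = 1.064, about 8 patients on 120. Going from 0.813 to 0.866 multiplies it by [(1.645 + 1.108)/(1.645 + 0.889)]² = 1.180, about 22 patients.

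**5. The plan's minimum-cases rule, 10·k/p.**

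| k | p = 0.28 | p = 0.40 | p = 0.47 |
|---|---|---|---|
| 2 (as stated) | 71.4 | 50.0 | 42.6 |
| 4 (two covariates added) | 142.9 | 100.0 | 85.1 |
| 5 (plus module interaction) | 178.6 | 125.0 | 106.4 |

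The first row reproduces the stated 71 and 43. With k = 4, 120 patients are enough at p = 0.40 and 0.47, but not at the 0.28 that the plan chose as its minimum.

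**The case against.** **The text does not exclude covariates.** Data analysis states the purpose of the regression, and k = 2 is an input to a rule of thumb, not a full list of terms. Combined exposure suggests an interaction that k = 2 also leaves out. It would therefore be too strong to say the plan rules out adjustment. What stands is narrower: the model is described through the modules alone, and the article gives these two variables a different, exploratory role. That is a stated choice and not a detail left to an analysis plan.

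**Prognostic value is not shown.** A reader might infer that the trial forfeits power it already has. The documents do not support this. The Background says one trial controlled for these variables, not that they predicted relapse or how strongly. That trial was in inpatients followed for a year; this one is in outpatients at three months. Being a moderator of bias change is also a different role from predicting relapse. This objection stands in full and limits the size of the claim.

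**No rival primary result is declared.** A reader might infer that the plan leaves an adjusted and an unadjusted primary result to choose between. The Abstract labels the moderator work exploratory, and the aims section says only that effects will be explored. An unadjusted randomised comparison is valid, and its error rate already allows for chance imbalance. If the better of the two results were nevertheless reported, simulation under the null puts the nominal 5% at about 6.4% for covariates with an odds ratio of 1.5 per SD and 7.3% at 2.0. That is a modest risk.

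**The rule and the covariate set.** Adjustment breaks the plan's own 10·k/p calculation at p = 0.28, and keeping the model small is defensible in a phase II trial. This stands as a cost to declare. Age and previous detoxifications are proposed because allocation does not balance them, whereas gender and medication category are balancing factors. The sponsor should still justify the final set.

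**Conclusion.** The point holds as a cheap improvement and not as an error. The stated odds ratio of 0.396 is correctly derived, and the unadjusted analysis is valid. Fixing the two covariates in advance would probably add about 0 to 3 points of power up to an odds ratio of 1.5 per SD each, and about 5 to 7 points at 2.0, with no material loss if they predict nothing. The direction is secure if the variables predict relapse. The size rests on an assumed prognostic strength, on two independent and normally distributed covariates, and on no effect of the other module.

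**What to change.** Add a sentence to Data analysis naming age and number of previous detoxifications as fixed continuous covariates in the primary logistic regression. Choose any transformation in advance, such as log(1 + x) for a skewed count. Declare the adjusted model primary and the unadjusted one supportive, and leave the moderator analyses exploratory.

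The costs are small but should be written down:

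- The odds ratio becomes conditional and lies further from 1 (for example 0.375 instead of 0.396 at a covariate odds ratio of 1.42). Report a standardised risk difference beside it.
- Restate the minimum-cases calculation with k = 4: 143 at p = 0.28 (above 120), 100 at p = 0.40, about 86 at p = 0.47. If a module interaction stays in the model, k = 5 needs 125 at p = 0.40. Say why the model is still acceptable.
- Specify a penalised likelihood fit in case events are few.

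No new data collection is needed.

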## Methods/Design

### Trial design

The present study is a phase II, double-blind, parallel group RCT. Following the design of previous CBM studies [18,19], participants complete 11 sessions of either the active or placebo version of both attentional and approach bias training modules. The experimental intervention has a 2×2 factorial design, which combines the active and placebo training modules into four experimental conditions: one double active training experimental condition, two experimental groups receiving one active training and one placebo training and one double placebo training control group. According to the experimental design, the probability of receiving at least one active CBM intervention reaches 75%. The placebo version of each training module consists of a continuous assessment, in which half of the trials train the cognitive biases away towards alcohol and the other half towards soda (active placebo). The manipulation of the stimulus-response contingency in each task allows for a controlled and clean comparison between experimental conditions while retaining the same tasks, stimuli and instructions. Also, Wiers *et al*. [18] found no differences between continuous assessment and no-training placebo conditions, which suggested that either type of placebo could be used.

Participants complete a total of 14 sessions: two baseline assessment sessions, 11 training sessions, one post-intervention assessment session and one three-month follow-up assessment session. Participants complete the training sessions with a between-session time interval of a maximum of five days. The post-intervention assessment takes place between the 10th and 11th training session during a ‘masked’ session (participants do not know they are completing the post-intervention evaluation). That is to avoid possible negative feelings related to the final ‘evaluation’ of the intervention and minimise self-presentation biases and/or preparatory strategies.

Participant flowchart as per Consolidated Standards of Reporting Trials (CONSORT) statement [27] is presented in Figure 1. The study was approved by the Ethics Committee of the School of Psychology of the University of Padova (March 2013; Protocol number: 1242) and registered at Current Control Trials (identifier: ISRCTN01005959).

**Figure 1 Fig1:**
[figure not shown]
**Participant flow diagram.**

### Participants and procedure

Participants are adult outpatients with a main diagnosis of alcohol addiction disorder, recruited from the public health addiction service (Servizio per le Dipendenze, ULSS10) of San Donà di Piave, Italy. The targeted number of recruited participants is 120, to be equally balanced across the four experimental conditions.

Participants are screened for eligibility according to the following criteria:Inclusion criteria: adult outpatients with primary diagnosis of alcohol addiction disorder according to the diagnostic criteria of the Diagnostic and Statistical Manual of Mental Disorders (4th Edition, Text Revision) and alcohol abstinence for at least two months.Exclusion criteria: neurocognitive problems, visual or hand-motoric handicaps, severe neurological disorders (such as Korsakoff syndrome), comorbidity with psychotic disorders or low fluency in the Italian language.

Participants are recruited by clinicians according to the inclusion and exclusion criteria and invited to participate in the study. At invitation, clinicians provide the patients with a brief introduction to the study by explaining that addiction disorders are partly due to uncontrolled and automatic processes which can substantially increase the risk for relapse, and that the main objective of the research is to test the effectiveness of new computerised treatment interventions, which can help the patient in gaining and increasing a better control over these underlying mechanisms. The clinician will also supervise patients’ activity and progress along both the patient’s standard treatment and the experimental intervention.

After the patients are informed about the research objectives and the norms for confidential data treatment and for participating in the study, interested participants undersign a written informed consent form and create their research account at the training website.

Participants will be excluded from the study if they do not complete the baseline assessment or if they disclose the intention to discontinue the study. All participants will continue their treatment as usual in the public addiction service. Upon completion of the three-month follow-up assessment, they have the opportunity to attend the double active CBM training if they wish. The percentage of participants that enter the booster training is registered.

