### Randomisation

Participants are automatically randomised at the pre-intervention stage across the four experimental conditions, stratified by gender and category of medication intake, as specified here under:CategoryA (alcohol agonists and antagonists): Disulfiram, Naltrexone, Acamprosate and Gamma-hydroxybutyrate;Category B (psychoactive medication such as anxiolytic, antidepressant and neuroleptic medications);Category C (other medications).

Participants are randomly allocated to one of the conditions to which the fewest participants of their gender and medication category have been so far assigned.

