A second strength of the present study bears the investigation of the combination of different CBM training with alcohol dependent outpatients. Up to now, the separate effects of CBM interventions have been mainly studied in samples of heavy drinkers [16,54] and residential inpatients [17-19], while the combined effects of multiple web-based CBM trainings are currently under investigation with a broader sample of at-risk and problematic drinkers [20]. Therefore, the second strength of the present study comes from the exploration of the potential effects of a CBM intervention in a different group of recipients who are also likely to benefit from the intervention. Alcohol dependent outpatients are usually characterised by cycles of relapses alternated with periods of abstinence, thus featuring their alcohol problems with a higher chronicity. When considering CBM modules as low-cost interventions that may potentially reduce the relapse rate and/or prolong the period of abstinence [17-19], therefore also prospectively deflating the number of patients that cyclically turn to addiction services to subside their relapse, the inclusion of CBM modules in the outpatient regimen of addiction interventions may be very cost-effective.

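### Duration of abstinence is recorded at baseline but is neither balanced in the randomisation nor included in the primary model as described, which forgoes modest precision and leaves chance imbalance uncorrected

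*Protocol article*

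**What the plan says.** All references are to the protocol article.

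- **Participants and procedure** sets the entry condition as "alcohol abstinence for at least two months". No maximum is given.
- **Baseline measures** lists the case-history items taken at registration: "duration of alcohol addiction, previous detoxifications and treatments, duration of current abstinence and medication intake". Abstinence duration is therefore available for every registered participant before training starts.
- **Randomisation** is "stratified by gender and category of medication intake", with each participant sent to a least-filled condition within those categories. Abstinence duration plays no part.
- **Data analysis** states the primary method: "a multiple logistic regression will be used to estimate how much the main and combined exposure to the two CBM modules affects the occurrence". The outcome modelled is any lapse or relapse by the three-month assessment. No baseline covariate is named.
- **Sample size** counts two independent variables (k = 2), the two training factors.
- The third research question in **Data analysis** names baseline bias strength and Stroop performance, "as well as age, gender and previous detoxifications, are hypothesised to moderate" the change in bias. Abstinence duration is not among them.
- **Aims and hypotheses** also promises to explore several clinical variables against the outcomes. That list is open-ended and does not name abstinence duration.
- **Discussion** says: "Alcohol dependent outpatients are usually characterised by cycles of relapses alternated with periods of abstinence".

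**The concern.** The criterion admits a patient ten weeks abstinent and a patient several years abstinent on equal terms. The primary outcome is a new lapse or relapse within three months of the intervention. Among the recorded case-history items, time already abstinent is the one measured on the scale closest to that outcome, so it is a natural candidate for adjustment.

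Each module effect rests on 60 against 60 patients, and the article says recruitment is capped at 120 by the supply of eligible outpatients. Precision therefore cannot be bought with more patients, and a baseline variable that is already collected is one of the few ways left to gain some. Without it, a chance difference in abstinence between the two levels of a module is neither prevented by the allocation nor corrected by the stated model.

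**Working it through.** **1. Reproduce the article's figure.** Inputs from Sample size: placebo relapse rate 0.60, odds ratio 0.396, n = 120 (60 v 60 per module), one-tailed, critical z = −1.645, power 0.80.

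- Active-arm odds: (0.60/0.40) × 0.396 = 0.594, so p₂ = 0.594/1.594 = 0.373.
- Wald test on the log odds ratio: variance = 1/(60 × 0.60 × 0.40) + 1/(60 × 0.373 × 0.627), and power = Φ(|ln 0.396|/SE − 1.645) = 0.795.
- Two-proportion formula: power 0.808, or 59 per level for 80%.
- Solving for 80% power gives 0.393 (Wald) and 0.400 (two proportions), which bracket 0.396.

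The stated figure is sound. It already comes from an unadjusted comparison, so leaving abstinence out does not push power below it.

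**2. What adjustment would add.** The article gives no association between abstinence duration and relapse, so its strength is assumed. Abstinence is represented by a standard-normal covariate with the odds ratio per SD shown below. The marginal rates are held at 0.60 and 0.373, so unadjusted power stays at 0.795 by formula. Adjusted power comes from the expected information matrix of the logistic model with intercept, module and covariate, and from 8,000 simulated trials per row.

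| OR per SD (assumed) | Conditional OR for module | Adjusted power, expected information | Simulated power, unadjusted → adjusted |
|---|---|---|---|
| 1 (not prognostic) | 0.396 | 0.795 | 0.804 → 0.812 |
| 1.5 | 0.382 | 0.806 | 0.799 → 0.820 |
| 2 | 0.359 | 0.824 | 0.803 → 0.843 |
| 2.5 | 0.336 | 0.840 | 0.794 → 0.859 |
| 3 | 0.316 | 0.854 | 0.800 → 0.880 |

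By expected information the gains are 1.1, 2.9, 4.5 and 5.9 points. The simulated gains are 2.1, 4.0, 6.6 and 8.0. The simulation also shows 0.8 of a point when the covariate does nothing, so the upper figures are slightly generous. A fair summary is 1 to 3 points for an odds ratio of 1.5 to 2, and 5 to 8 points for 2.5 to 3.

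The article also cites a placebo rate of 0.18, which it sets aside. At that rate unadjusted power for 0.396 is about 0.48, and the gain by expected information is about 1 to 4 points.

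**3. Type I error.** With no module effect, simulated one-sided error was about 0.05 to 0.06 unadjusted and about 0.05 adjusted, for covariate log odds ratios from 0 to 1.5 per SD. There is no material inflation in either analysis.

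**4. Chance imbalance.** The SD of the difference in covariate means for 60 v 60 is √(2/60) = 0.183 SD, and 1.96 × 0.183 = 0.36 SD. A difference at least that large occurs in 5% of trials per module. To first order it shifts the log odds by 0.358 × ln(OR):

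- OR 1.5: 0.145
- OR 2: 0.248
- OR 3: 0.393

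Against the target |ln 0.396| = 0.926, these are 16%, 27% and 42%.

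**5. Room in the model.** The article's rule is 10 × k/p with p = 0.28:

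- k = 2: 20/0.28 = 71.4
- k = 3 (two modules plus abstinence): 30/0.28 = 107.1
- k = 4 (adding the interaction): 40/0.28 = 142.9

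The main-effects model with abstinence fits within 120. The model that also carries the interaction does not.

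**The case against.** The strongest reply is that this is one more covariate in a model whose details may sit in an analysis plan that is not shown. The k = 2 in Sample size is a minimum-cases heuristic, not a model specification. It does not even count the combined exposure that Data analysis includes. Data analysis names no covariates but rules none out, and the open list under Aims and hypotheses leaves room for exploratory use of abstinence. All this is fair, and it is why the point concerns the model as described. It does not remove the point: the article names its balancing factors, primary predictors and moderators, and abstinence duration is in none of them.

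Second, a reader might infer that abstinence duration is a strong driver of relapse. The documents do not support that. The Discussion describes cycles of relapse and abstinence but gives no association and no direction. The covariates named elsewhere have a stated precedent, because the Background reports that earlier trials controlled for gender, or for age and previous detoxifications. The size of the benefit is therefore an assumption throughout.

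Third, a reader might call the omission a bias. It is not. Randomisation balances abstinence in expectation, and the significance level already allows for chance imbalance. What remains is that, in a given trial, a visible imbalance would have no planned correction.

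Fourth, adjustment has two costs. The adjusted odds ratio is conditional and no longer maps directly onto 0.396. The article's own case rule also excludes abstinence and the interaction from the same model. Both objections stand, and both shape the fix.

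**Conclusion.** The point holds as a modest efficiency matter. A baseline variable close to the outcome is collected, but it is used neither in the allocation nor in the primary model as described. Under assumed prognostic strength, adjusting gains about 1 to 3 power points for an odds ratio of 1.5 to 2 per SD and about 5 to 8 for 2.5 to 3. It loses essentially nothing if the variable is not prognostic. An imbalance of 0.36 SD or more, with a 5% chance per module, would go uncorrected.

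These figures rest on a normally distributed covariate, a linear effect on the log odds, all 120 participants analysed and a placebo rate of 0.60.

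Three further readings are not supported. The entry criterion is not at fault, since a two-month minimum without a ceiling is a legitimate choice. The 0.396 is not wrong. Nor is it right that the trial can say nothing about recently abstinent patients: the data will exist, but no such analysis is named.

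**What to change.** Before unblinding, prespecify baseline duration of current abstinence, as log months and continuous, as a covariate in the main-effects primary logistic model with the two modules. Examine the module-by-module interaction in a separate model. State that the adjusted odds ratio is conditional, and also report a standardised marginal effect so that the result can be set beside 0.396. Treat any analysis of abstinence duration as a moderator as exploratory only. Leave eligibility unchanged.

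The cost is one line in the analysis plan and one degree of freedom, with no new data collection. By the article's rule, the requirement rises from about 71 to about 107 cases. That leaves 120 − 107 = 13 participants (11%) as the margin for attrition, and the statement that the sample allows for high attrition should be reworded to match.
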